#### Statistical analysis

The prevalence of PoPH will be examined at the time of PoPH diagnosis. The clinical pathophysiology of PoPH will be evaluated by multivariate analysis using the following factors: etiology of liver disease, age, sex, height, weight, diagnosis, medication history, smoking history, drinking history, NYHA classification, 6-minute walking distance, laboratory tests, FibroScan^®^ results, the presence of cancer, right heart catheter findings (mean pulmonary artery pressure, right atrial pressure, pulmonary artery wedge pressure, and cardiac index), and echocardiographic findings. The changes in clinical symptoms, UCG findings, and hepatic function will be also be examined before and after treatment. Continuous variables will be statistically evaluated by means of the Mann–Whitney U test, while categorical variables will be analyzed using the chi-square test.

Overall survival rate will be examined using the Kaplan–Meier method. Independent factors influencing overall survival will be assessed by Cox regression analysis with stepwise methods.

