Right ventricle:left ventricle basal diameter ratio >1.0	Right ventricular outflow doppler acceleration time <105 msec and/or midsystolic notching	Inferior cava diameter >21 mm with decreased inspiratory collapse (<50% with a sniff or <20% with quiet inspiration)
Flattening of the interventricular septum (left ventricular eccentricity index >1.1 in systole and/or diastole)	Early diastolic pulmonary regurgitation velocity >2.2 m/sec	Right atrium area (end-systole) >18 cm^2^
	Pulmonary artery diameter >25 mm	

Abbreviations: PAH, pulmonary artery hypertension.

**Table 5 pone.0249435.t005:** Diagnosis criteria of PoPH [21–23].

1. Existence of PAH by right heart catheraization
a. Mean pulmonary artery pressure (mPAP) ≥ 25mmHg
b. Pulmonary artery wedge pressure (PAWP) ≤ 15mmHg
2. Existence of portal hypertension
Hepatic vein pressure gradient (HVPG) ≥ 5mmHg
3. Rule out of other etiology of PAH

Abbreviations: PoPH, portopulmonary hypertension; PAH, pulmonary artery hypertension.

When a PoPH diagnosis is made, the following clinical data will be collected: etiology of liver disease, age, gender, height, body weight, history of medication, drinking habit, smoking habit, New York Heart Association (NYHA) classification, 6-minute walking distance, FibroScan^®^ results, blood and urine data, thoracic-abdominal enhanced computed tomography findings, right heart catheter findings (mean pulmonary artery pressure, right atrial pressure, pulmonary artery wedge pressure, cardiac index, cardiac output, pulmonary vascular resistance, and mixed venous oxygen saturation), and echocardiographic findings.

Upon diagnosis, PoPH treatment will be initiated by a cardiologist based on the guidelines for pulmonary hypertension issued by the Japanese Circulation Society [22]. Patients will be evaluated every six months for blood and urine findings, abdominal ultrasonography results, and clinical symptoms. UCG will be performed on a yearly basis. The observation period will be five years from the time of patient enrollment and will end if the patient dies or becomes lost to follow-up. Ultimately, the 5-year survival rate of PoPH patients and factors associated with survival will be analyzed (Observational study 3).

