### Statistical considerations

#### Sample size estimation

As the exact prevalence of PoPH remains unknown, we planned to screen all patients regularly visiting our department for chronic liver disease observation or treatment. Approximately 4,800 patients visit our department yearly in addition to 300 new patient referrals. Symptoms indicating PoPH have been found in roughly half of patients with chronic liver disease in the outpatient questionnaire. Assuming that 20% of patients will decline informed consent, we aim to recruit 2,500 cases with chronic liver disease.

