## Discussion

This prospective observational study aims to clarify the clinical characteristics of PoPH in the Japanese population. Both cirrhosis and non-cirrhosis stage patients may become complicated with PoPH. Although the frequency of PoPH in patients with cirrhosis has been described, PoPH prevalence in chronic liver disease remains unknown. Unlike in cohorts from Western countries, where the proportion of ALD is high [24], viral hepatitis-related chronic liver disease is more prevalent in Japan. In the few studies on PoPH in Asia and Japan investigating disease prevalence and incidence, AIH and PBC were found to be more likely complicated with PoPH [5]. However, due to the small number of cases included in those investigations, the clinical picture of PoPH is uncertain. The present study will seek to answer these important questions.

A retrospective study from the United States showed that patients untreated for PoPH had a poor 5-year survival rate of 14%, which was associated with the delayed diagnosis of PoPH [25]. One reason could be that up to 60% of patients with PoPH were asymptomatic [1]. PoPH cases are contraindicated for liver transplantation due to high operative mortality and poor prognosis. Early intervention for PoPH is therefore essential to overcome this issue and improve prognosis. An established standardized questionnaire may be helpful in PoPH screening as a first diagnostic step.

During the past two months, this study’s questionnaire has been administered to 300 patients with chronic liver disease meeting the inclusion criteria. Interestingly, 153 patients (51.0%) described symptoms suggestive of PoPH. Among them, 36 patients providing informed consent underwent further UCG analysis. Two cases were found to have PAH, while one case was diagnosed as having PoPH. As previously reported, the prevalence of PoPH is expected to be very low. By recruiting a sufficient number of patients, however, we aim to determine the actual status of PoPH in Japan.

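### Before/after-treatment changes are measured in the same patients, but the only tests the plan names are for independent groups

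*Protocol article*

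**What the plan says.** All references are to the protocol article. Under Statistical analysis, after the multivariate analysis of clinical pathophysiology, the plan states: "The changes in clinical symptoms, UCG findings, and hepatic function will be also be examined before and after treatment". The sentence after it reads: "Continuous variables will be statistically evaluated by means of the Mann–Whitney U test, while categorical variables will be analyzed using the chi-square test". It is general: it neither mentions the before/after comparison nor exempts it. The only other methods in the section are an unspecified multivariate analysis, Kaplan–Meier and stepwise Cox regression. No signed-rank, McNemar or repeated-measures method appears.

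The data structure is given under Trial design and follow-up. Treatment follows directly on diagnosis: "Upon diagnosis, PoPH treatment will be initiated by a cardiologist based on the guidelines for pulmonary hypertension issued by the Japanese Circulation Society". The same patients are then measured again: "Patients will be evaluated every six months for blood and urine findings, abdominal ultrasonography results, and clinical symptoms", with echocardiography repeated yearly. No untreated comparison group is described.

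**The concern.** A before/after contrast in treated PoPH patients is a within-patient contrast. Mann–Whitney U and chi-square treat the two sets of values as if they came from different people. They ignore the pairing, and their reference distributions assume an independence that does not hold. When a patient's earlier and later values are positively correlated, as repeated measurements on one person usually are, the variability the test allows for exceeds the true variability of the change. The test then rejects too rarely. Few PoPH patients are likely, so information discarded in this way could hide a real change after treatment.

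**Working it through.** **No figure to reproduce.** The article gives no significance level, number of pairs, effect size, SD or within-patient correlation for this comparison. Everything numerical below is therefore an assumption, shown over a range.

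**How many pairs?** The number is not stated. It can only be bracketed.
- The target is stated as "we aim to recruit 2,500 cases with chronic liver disease". The Discussion reports an early yield from 300 questionnaires and 36 echocardiograms: "Two cases were found to have PAH, while one case was diagnosed as having PoPH".
- Applying 1/300 to 2,500 gives 2,500/300 ≈ 8.
- Applying 1/300 to the yearly pool (4,800 + 300 = 5,100) gives 5,100/300 = 17.
- Applying 1–2%, the Introduction's figure for cirrhosis, to 2,500 gives 25 to 50.
- Applying 1/36 to 2,500 gives 2,500/36 ≈ 69.

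The 16 and 25 pairs used below lie inside this range. They are not figures from the plan.

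**Direction, from the variance.** Let before and after values have a common SD σ and correlation ρ, with n pairs. The true variance of the mean change is 2σ²(1−ρ)/n. An independent-groups test works as if it were 2σ²/n. In the normal approximation, the effective critical value is 1.96/√(1−ρ) instead of 1.96:
- ρ = 0.3: 1.96/0.837 = 2.34, actual two-sided size about 1.9%
- ρ = 0.5: 1.96/0.707 = 2.77, actual size about 0.6%
- ρ = 0.7: 1.96/0.548 = 3.58, actual size about 0.03%

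This is exact only for a z-type comparison of means, but it gives the direction and rough size.

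**Simulation 1: fixed change.** Bivariate normal pairs, n = 16, change 0.5 SD, nominal two-sided 5%.

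| ρ | Mann–Whitney power | Signed-rank power | Share of power lost | Mann–Whitney actual size |
|---|---|---|---|---|
| 0.3 | 22% | 32% | 1 − 22/32 = 31% | about 2% |
| 0.5 | 21% | 42% | 1 − 21/42 = 50% | about 1% |
| 0.7 | 16% | 65% | 1 − 16/65 = 75% | about 0.2% |

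The signed-rank test keeps a size of about 4–5%.

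**Simulation 2: change scaled so that a paired analysis has about 80% nominal power.** 4,000 runs, n = 25.

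| ρ | Mann–Whitney power | Signed-rank power | Share of power lost |
|---|---|---|---|
| 0 | 0.75 | 0.74 | none |
| 0.3 | 0.60 | 0.74 | 1 − 0.60/0.74 = 19% |
| 0.5 | 0.46 | 0.74 | 1 − 0.46/0.74 = 38% |
| 0.7 | 0.19 | 0.74 | 1 − 0.19/0.74 = 74% |

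The pattern is similar at 17, 50 and 69 pairs. At 8 pairs the signed-rank test itself reaches only about 0.60.

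**Categorical items.** One binary symptom, assumed present in 70% before and 40% after, n = 25. Uncorrected chi-square against exact McNemar:
- ρ = 0: 0.62 against 0.44
- ρ = 0.3: 0.64 against 0.59
- ρ = 0.5: 0.65 against 0.76
- maximum feasible correlation: 0.66 against 0.81

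The largest loss here is 0.81 − 0.66 = 0.15. At low correlation chi-square rejects more often, because exact McNemar is itself conservative with few discordant pairs.

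**The case against.** The strongest reply is that the test sentence never says it governs the before/after comparison. The paragraph opens with the pathophysiology work, where Mann–Whitney and chi-square would be ordinary between-group tests, and it says only that changes will be examined. On that reading the before/after method is simply not stated, and a condensed article may leave it to a fuller document. The link does rest on adjacency and general wording. It is not an explicit assignment, and that much of the reply stands. It does not dispose of the point. The sentence covers continuous and categorical variables without limit, it follows directly on the before/after sentence, and the paragraph describes no explicit two-group comparison that it could belong to instead. A fuller analysis plan that followed this text would carry the mismatch forward.

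A reader might also infer that the named tests lose most of the power. The documents do not support that. They give no within-patient correlation. In the simulations a loss of most of the power appears for Mann–Whitney only at correlations of roughly 0.6 or more, and it was not seen for chi-square in the scenario tried.

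Finally, before/after change is neither an endpoint nor one of the three research questions. The error for continuous variables is conservative, so it would not create false claims of benefit. With very few patients the comparison is weak whichever test is used. All three points stand and limit the severity.

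**Conclusion.** The point holds in a limited form. The plan describes a within-patient comparison, and the only tests its wording makes available for that comparison assume independent groups. For continuous measures the resulting p-values are too large at any positive within-patient correlation. The loss of power runs from modest at correlation 0.3 to severe at 0.7. These sizes rest on assumed normal data, number of pairs, size of change and correlation. For categorical measures the independence assumption is violated, but no large power loss is shown. Severity is minor to moderate: the primary endpoint (prevalence and etiology) and the secondary endpoint (5-year survival) do not depend on these tests, so a reader should not take this as a threat to the main results.

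**What to change.** Replace the general test sentence with one that separates the two kinds of comparison:
- **Before/after treatment:** Wilcoxon signed-rank test for continuous or ordinal measures (NYHA class, for example, if it is recorded again), reported with the median change and its confidence interval. McNemar's exact test for binary symptoms.
- **Between groups:** Mann–Whitney U and chi-square, restricted to comparisons of different patients.

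A mixed model using the six-monthly and yearly visits is optional and may be hard to support if few patients are diagnosed. The cost is one sentence. Recruitment, visits and data collection do not change, and the edit can be made before any follow-up data are analysed.

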#### Etiology of chronic liver diseases

The etiologies of the chronic liver diseases included in this study are as follows: 1) hepatitis B virus (HBV) infection defined as HBe antigen-positive asymptomatic carriers, chronic hepatitis, HBe antigen-negative inactive carriers, and HBs antigen-negative clinical remission regardless of cirrhosis status, according to the guidelines provided by the Japan Society of Hepatology [14], 2) HCV infection including patients with persistent HCV infection and with post-HCV eradication in a sustained virological response, based on the guidelines provided by the Japan Society of Hepatology [15], 3) ALD including patients with a drinking habit (ethanol >60 g/day for men, ethanol >40 g/day for women) and persistent elevation of aminotransferase and γ-GTP, according to the guidelines established by the Japanese Society of Gastroenterology [16], 4) nonalcoholic fatty liver disease (NAFLD)/nonalcoholic steatohepatitis (NASH), according to the guidelines provided by the Japanese Society of Gastroenterology and the Japan Society of Hepatology [17], and 5) autoimmune liver disease including AIH, primary biliary cholangitis (PBC), and primary sclerosing cholangitis (PSC), based on the guidelines provided by the Japan Society of Hepatology [18–20].

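### The chi-square test is named for categorical variables, although roughly 8–25 expected PoPH cases leave many etiology tables too sparse for it

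*Protocol article*

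**What the plan says.** Under Statistical analysis, the protocol article assigns the Mann–Whitney U test to continuous variables and states that "categorical variables will be analyzed using the chi-square test". No exact test and no continuity correction is mentioned. Under Endpoints, the etiology of PoPH is part of the primary endpoint, together with prevalence. Under Etiology of chronic liver diseases there are five groups: HBV, HCV, ALD, NAFLD/NASH and autoimmune disease, the last combining AIH, PBC and PSC. The Introduction singles out AIH, and the Discussion AIH and PBC, as possibly linked to PoPH.

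On numbers, Sample size estimation says "we aim to recruit 2,500 cases with chronic liver disease", and the Discussion says that "the prevalence of PoPH is expected to be very low". The Discussion also reports early results: the "questionnaire has been administered to 300 patients with chronic liver disease", 153 had symptoms, 36 had echocardiography and one was diagnosed with PoPH. The Introduction cites an earlier Japanese series with 2 PoPH cases in 186 patients (1%).

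**The concern.** The chi-square test relies on a large-sample approximation that becomes poor when expected cell counts are small. Here the number of PoPH cases limits every comparison, and the article itself predicts that it will be small. If the p-value is unreliable, one chance PoPH case in an uncommon liver disease could be reported as an etiologic association. That would be a false signal within the primary endpoint, in a field where the article says earlier studies were too small to give a clear picture.

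**Working it through.** **Inputs.** From the article: target 2,500; one PoPH case in 300 questionnaires, 153 symptomatic patients or 36 echocardiograms; 1% in the earlier series; five etiology groups. Assumed, because the article does not give them: etiology shares, a two-sided 5% level and an uncorrected Pearson test. The article plans no case count, so there is none to reproduce.

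**Step 1: expected PoPH cases.**
- 2,500 × 1/300 = 8.3
- 2,500 × 1/153 = 16.3
- 2,500 × 1% = 25
- 2,500 × 1/36 = 69

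Applying 1/300 to the 4,800 + 300 = 5,100 patients seen gives 17. I use 8, 17 and 25. The range is uncertain: the exact 95% interval for 1/300 corresponds to 0.2 to 46 cases in 2,500.

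**Step 2: when expected counts fall below 5.** Expected PoPH cases in a group = cases × share. This is below 5 when the share is below 5/cases:
- 8 cases: below 62.5%. At least four of the five groups must qualify.
- 17 cases: below 29.4%. At least two must qualify, since four groups at 29.4% would exceed 100%.
- 25 cases: below 20%. At least one must qualify unless all five are exactly equal.
- 69 cases: below 7.2%.

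This step needs no assumption about shares.

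**Step 3: one worked table.** Take 8 cases, a diagnosis with a 2% share (50 of 2,500) and one PoPH case in it. The cells are 1, 7, 49 and 2,443.

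Chi-square = 2,500 × (1 × 2,443 − 7 × 49)² / (8 × 2,492 × 50 × 2,450) = 4.51, p = 0.034.

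Fisher's p is the chance of at least one case in the diagnosis, about 1 − 0.98⁸ = 0.149. Because any count of one or more is declared significant, the Pearson test's false-positive rate in this table is also 14.9%.

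**Step 4: false-positive rates, one diagnosis against the rest, N = 2,500.** "Fixed" holds the case count and group size (hypergeometric enumeration). "Varying" averages over a binomial case count with that mean.

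| Cases | Assumed share | Pearson, fixed | Pearson, varying | Fisher, fixed |
|---|---|---|---|---|
| 8 | 2% | 14.9% | 7.6% | 1.0% |
| 17 | 1% | 15.8% | 8.2% | 1.2% |
| 25 | 0.5% | 11.4% | 11.2% | 0.6% |
| 8 | 0.5% | 3.8% | 3.8% | 3.8% |
| 17 | 2% | 4.4% | 4.7% | 4.4% |
| 25 | 1% | 2.5% | 3.4% | 2.5% |
| 8 / 17 / 25 | 3% (AIH) | 2.2 / 9.0 / 3.7% | 6.5 / 5.5 / 4.4% | 2.2 / 1.3 / 3.7% |
| 8 / 17 / 25 | 6% (PBC) | 7.9 / 7.8 / 5.9% | 5.6 / 4.4 / 4.0% | 1.0 / 1.6 / 1.5% |

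With varying counts, shares of 5–30% give a median of 4.4% and a maximum of 5.5%.

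**Step 5: overall tests across etiologies (simulation).** For the five groups, the size is about 3.7–6.6% across the assumed share patterns. If AIH, PBC and PSC are separated (assumed 3%, 6% and 1%), it is about 10–11% with 8 cases and about 6–6.5% with 17 or 25.

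**Step 6: within the PoPH group.** With 8 patients split 4 and 4 and three positives, all three fall on one side with probability 2 × 5/70 = 14.3%. Pearson then gives 8 × 12² / (4 × 4 × 3 × 5) = 4.8, p = 0.03, while Fisher gives p = 0.143. If the total number of positives is not fixed, the size for 4 versus 4 is 7.0% at an event probability of 0.5 and 2.4% at 0.2.

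**The case against.** A reader might infer that the planned test has about twice its nominal error rate in general. The documents do not support that. Rates of that order need a diagnosis with about 2% of patients or fewer, and even then only some pairings of share and case count produce them. No shares are stated. At plausible assumed shares for AIH and PBC, the two diagnoses the article singles out, the error is near nominal once the case count varies, and one case is not enough for significance: at least two are needed. On the article's own five groups the overall test behaves well. A continuity correction, on which the article is silent, would also hold the two-by-two error below 5%. All of this stands, and it limits the size of the point.

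It can also be said that a journal article leaves the handling of small counts to an analysis plan that is not shown, that it does not say the chi-square test is the only one, and that the study is descriptive with no confirmatory test of etiology. This carries less weight. The article does name a method, without qualification, for data that it expects to be very sparse, and etiology is in the primary endpoint. As written, the result for a rare diagnosis could turn on whether the software applies a correction by default.

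The 8–25 range is derived and is not stated in the article. The 1/36 figure would give about 69 cases and ease the problem for all but the smaller groups.

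**Conclusion.** The point holds in a limited form. Expected counts below 5 are close to certain for some etiology comparisons, whatever the shares, so a chi-square test without a small-count rule suits the predicted data poorly. Under assumed shares of about 2% or less, the uncorrected Pearson test can reach about 8–11% when the case count varies, and about 15% for some fixed counts. For assumed shares of 3–6% it is about 4–6.5%, and for the five broad groups it is close to 5%. These sizes rest on a 5% level, no continuity correction, 8–25 cases and a cohort of 2,500. The change is worth making because it is cheap and protects part of the primary endpoint, not because most comparisons would be badly wrong.

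**What to change.** In Statistical analysis, state that Fisher's exact test replaces the chi-square test when any expected count is below 5, with the Fisher–Freeman–Halton test or a Monte Carlo exact p-value for more than two categories. Expected counts depend only on the row and column totals, so this rule does not let the observed association choose the test. Report PoPH prevalence by etiology with exact confidence intervals as the main etiology result; these show directly how little a single case establishes.

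The cost is one or two sentences and standard software. The drawback is that exact tests are somewhat conservative: in the table above Fisher's size is between 0.6% and 4.4%. A mid-p version, named in advance, would reduce this.

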## Discussion

This prospective observational study aims to clarify the clinical characteristics of PoPH in the Japanese population. Both cirrhosis and non-cirrhosis stage patients may become complicated with PoPH. Although the frequency of PoPH in patients with cirrhosis has been described, PoPH prevalence in chronic liver disease remains unknown. Unlike in cohorts from Western countries, where the proportion of ALD is high [24], viral hepatitis-related chronic liver disease is more prevalent in Japan. In the few studies on PoPH in Asia and Japan investigating disease prevalence and incidence, AIH and PBC were found to be more likely complicated with PoPH [5]. However, due to the small number of cases included in those investigations, the clinical picture of PoPH is uncertain. The present study will seek to answer these important questions.

A retrospective study from the United States showed that patients untreated for PoPH had a poor 5-year survival rate of 14%, which was associated with the delayed diagnosis of PoPH [25]. One reason could be that up to 60% of patients with PoPH were asymptomatic [1]. PoPH cases are contraindicated for liver transplantation due to high operative mortality and poor prognosis. Early intervention for PoPH is therefore essential to overcome this issue and improve prognosis. An established standardized questionnaire may be helpful in PoPH screening as a first diagnostic step.

During the past two months, this study’s questionnaire has been administered to 300 patients with chronic liver disease meeting the inclusion criteria. Interestingly, 153 patients (51.0%) described symptoms suggestive of PoPH. Among them, 36 patients providing informed consent underwent further UCG analysis. Two cases were found to have PAH, while one case was diagnosed as having PoPH. As previously reported, the prevalence of PoPH is expected to be very low. By recruiting a sufficient number of patients, however, we aim to determine the actual status of PoPH in Japan.

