The clinical manifestations of PoPH are identical to those of PAH, i.e., dyspnea on exertion, atypical chest pain, elevated jugular venous pressure, leg edema, and others [1, 13], all of which are considered non-specific symptoms of PoPH. Therefore, the threshold for suspecting PoPH should be low since patients with chronic liver disease often exhibit dyspnea for a variety of reasons; a precise but simple medical history interview is needed for selecting candidate patients for ultrasonic echocardiography (UCG) and further examination. Moreover, as complicating PoPH in patients with chronic liver disease is a poor prognostic factor despite targeted therapy intervention [11], early detection and intervention is needed to improve prognosis in Japanese patients with PoPH.

The present study aims to address the following clinical research questions in Japanese patients with chronic liver disease:

Observational study 1: What is the prevalence of PoPH in Japanese patients with chronic liver disease?Observational study 2: What are the etiology of liver disease and clinical pathophysiology of PoPH?Observational study 3: What is the 5-year survival rate of PoPH, and which factors influence overall survival?

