#### Inclusion criteria

Patients in the analysis must meet all three inclusion criteria, as follows: 1) over 20 years of age, 2) having chronic liver disease, and 3) having symptoms suggestive of PoPH, as summarized in Table 1.

**Table 1 pone.0249435.t001:** Inclusion and exclusion criteria.

Inclusion criteria
Patients must meet all of the following items:
1. Age >20 years
2. Having chronic liver disease
3. Having any symptom indicating portopulmonary hypertension
Exclusion criteria
Patients with any of the following items are excluded:
1. Having history of chronic heart failure
2. Having history of pulmonary arterial hypertension from any other cause.
3. Unable to be followed at our hospital

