### Trial design and follow-up

Participant registration for the study will run from October 1, 2020 to October 30, 2022. All participants will answer the written questionnaire described in Table 2 in the outpatient clinic of Shinshu University Hospital. If at least one question is positive, informed consent will be obtained from the individual for enrollment in the study. Then, the participant will undergo ultrasound echocardiography (UCG) as a first-line screening. If the participant exhibits UCG-positive findings indicating a high probability of PoPH as shown in Tables 3 and 4, the patient will be referred to a cardiologist in the Department of Cardiology for further evaluation, whereby a definitive diagnosis will be made by right heart catherization findings as shown in Table 5. The frequency of PoPH patients will be analyzed (Observational study 1) along with the etiology of PoPH in chronic liver disease (Observational study 2).

**Table 2 pone.0249435.t002:** Standardized questionnaire on symptoms suggesting portopulmonary hypertension (translated from Japanese; respondents indicate “yes” or “no”).

1) Do you feel you cannot work comparably to other people of the same age and gender?
2) Do you feel you cannot move as fast as other people do?
3) Do you feel you cannot move at the same pace as others?
4) Do you need rest when climbing stairs or carrying heavy loads?
5) Do you ever experience shortness of breath?
6) Do you ever experience faintness?
7) Do you ever experience tiredness and/or persistent malaise?
8) Do you ever experience dizziness and/or vertigo?
9) Do you ever experience facial edema and/or pretibial edema?

**Table 3 pone.0249435.t003:** Echocardiographic probability of PAH in patients having symptoms indicative of PAH [21].

Peak tricuspid regurgitation velocity (m/s)	Presence of other echo PH signs	Echocardiographic probability of PAH
≤2.8	No	Low
≤2.8	Yes	Intermediate
2.9–3.4	No	
2.9–3.4	Yes	High
>3.4	Not required	

Abbreviations: PAH, pulmonary artery hypertension; PH, pulmonary hypertension.

**Table 4 pone.0249435.t004:** Echocardiographic signs suggesting PAH used to assess the probability of PAH in addition to tricuspid regurgitation velocity measurement in Table 3 [21].

A: Ventricles	B: Pulmonary artery	C: Inferior vena cava and right atrium

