#### Endpoints

The primary endpoint in this study is the prevalence of PoPH in Japanese patients with chronic liver disease and its etiology (Observational study 1 and study 2). The secondary endpoint is the overall 5-year survival rate (Observational study 3).

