## Conclusions

This study will reveal the prevalence and etiology, as well as the 5-year survival rate, of PoPH in Japanese patients with chronic liver disease.

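### The endpoint and conclusions promise PoPH prevalence and survival across chronic liver disease, but the design can identify only symptomatic, screen-detected PoPH, over a denominator the article leaves unclear

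*Protocol article*

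**What the plan says.** The promise carries no symptom restriction. Endpoints: "The primary endpoint in this study is the prevalence of PoPH in Japanese patients with chronic liver disease and its etiology", with overall 5-year survival as secondary endpoint. Conclusions: "This study will reveal the prevalence and etiology, as well as the 5-year survival rate, of PoPH in Japanese patients with chronic liver disease". The Discussion paragraph of the Abstract and the end of Trial design and follow-up are equally unrestricted.

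The route to a diagnosis is narrow:

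- Table 1, inclusion: "3. Having any symptom indicating portopulmonary hypertension".
- Trial design and follow-up: "If at least one question is positive, informed consent will be obtained from the individual for enrollment in the study". UCG comes only after that step.
- Same section: "If the participant exhibits UCG-positive findings indicating a high probability of PoPH as shown in Tables 3 and 4", the patient goes to a cardiologist, "whereby a definitive diagnosis will be made by right heart catherization findings as shown in Table 5".

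Table 3 grades UCG as low, intermediate or high probability. The Abstract words the referral trigger more loosely, as UCG findings that point to pulmonary hypertension.

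The Discussion then explains late diagnosis: "One reason could be that up to 60% of patients with PoPH were asymptomatic [1". The article describes no sampling of questionnaire-negative patients and no adjustment for them, and it does not name the restriction as a limitation.

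**The concern.** A patient who answers no to all nine items cannot be found to have PoPH in this study. By the article's own figure, those patients may include a large share of the cases. A second loss can occur at UCG if only the high-probability class is referred. Cases lost at either step are lost systematically, so the Discussion's reliance on recruiting enough patients reduces random error but not this error.

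At stake is what the study can conclude. The Introduction takes the low Japanese figures as a sign of underestimation. A result that omits silent disease cannot test that. The survival cohort consists only of patients who passed both steps, so its 5-year survival describes them and not PoPH in general.

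**Working it through.** **Inputs**

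- *a*, share of PoPH without symptoms: at most 0.60 (Discussion). The values 0.40 and 0.20 are assumptions, used to show the range.
- *q*, chance that such a case still answers yes to at least one item: not given. *q* = 0 is the worst case; *q* = 0.51 assumes the pilot's background rate.
- Pilot (Discussion): 300 questioned, 153 positive, 36 consented and had UCG, 1 PoPH.
- Source population (Sample size estimation): 4,800 + 300 = 5,100, about half symptomatic, so 2,550.

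**1. The plan's own figure.** 153/300 = 51.0%, as stated. The recruitment target of 2,500 does not enter the calculation.

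**2. Capture by the questionnaire.** Captured share = (1 − a) + a × q, taking every symptomatic case to answer yes at least once, and before any UCG loss.

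| a | q = 0 | q = 0.51 |
|---|---|---|
| 0.60 | 0.40 | 0.40 + 0.60 × 0.51 = 0.706 |
| 0.40 | 0.60 | 0.60 + 0.40 × 0.51 = 0.804 |
| 0.20 | 0.80 | 0.80 + 0.20 × 0.51 = 0.902 |

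At a = 0.60 the understatement over all respondents is 1/0.40 = 2.5-fold to 1/0.706 = 1.42-fold.

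**3. Effect of the denominator.** Assume a true prevalence of 1% in 5,100 (51 cases), a = 0.60, perfect UCG and full consent.

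| | Cases found | Over all 5,100 | Over the symptomatic 2,550 |
|---|---|---|---|
| q = 0 | 51 × 0.40 = 20.4 | 0.40% | 0.80% |
| q = 0.51 | 51 × 0.706 = 36.0 | 0.71% | 1.41% |

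Over all respondents the result is always below 1%. Over symptomatic patients it falls on either side. With q = 0, an assumed true 0.5% reads 0.20% or 0.40%, and an assumed 2% reads 0.80% or 1.60%.

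**4. Dividing by sensitivity.** Over all respondents, 0.40%/0.40 and 0.71%/0.706 both return 1.0%. Over symptomatic patients, 0.80%/0.40 and 1.41%/0.706 both give 2.0%, twice the assumed truth, because that denominator has already been halved.

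**5. Pilot.** 1/300 = 0.33%, 1/153 = 0.65%, 1/36 = 2.8%, a spread of 300/36 = 8.3-fold. One case supports no estimate; it only shows how much the denominator matters.

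**6. Which denominator the article means.** The Abstract has 2,500 patients completing the questionnaire. Sample size estimation presents 2,500 as recruits after discussing symptoms and refusal. Inclusion criteria requires everyone analysed to have symptoms, yet the Discussion describes the 300 pilot patients as meeting the criteria although only 153 had symptoms. The text supports either reading.

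**The case against.** The symptom requirement is disclosed in the Abstract, Table 1 and the design section, and the questionnaire is broad: one yes among nine items, including tiredness, dizziness and edema, is enough. Some cases called asymptomatic in the cited source will pass it. The 60% is an upper limit, and how that source defined asymptomatic is unknown. All of this stands and is why a range is given. None of it restores the unrestricted claim, because disclosing who is enrolled does not widen what is estimated.

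A reader might infer more than the article supports:

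- *That the result is simply a lower bound, 2.5 times too small.* This holds only over all respondents and at the extreme of the range. Over symptomatic patients it may be too high.
- *That the study repeats the error of earlier Japanese data.* The 186 patients in the Introduction all had catheterization, and no symptom or UCG selection is described for them.
- *That the Introduction's statement that "the threshold for suspecting PoPH should be low" contradicts the UCG step.* That sentence concerns whom to send to UCG, and the broad questionnaire satisfies it.
- *That the intermediate UCG class certainly has no route to catheterization.* The text gives none, but the flowchart is not shown, and the Abstract's wording could include that class.
- *That survival is biased in a known direction.* The article gives nothing from which to derive one.
- *That screen-negative patients are formally counted as free of PoPH.* The article does not say how they are counted.

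**Conclusion.** The point holds as a mismatch between the quantity promised and the quantity the design can identify. The study can estimate the frequency and survival of symptomatic, screen-detected PoPH. It cannot estimate either for PoPH in chronic liver disease as a whole.

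The size is conditional. Over all questionnaire respondents, taking the catheterization diagnosis as specific, the estimate is a lower bound. First-step capture is 40% to 71% if the asymptomatic share is 60%, and 80% to 90% if it is an assumed 20%. Any UCG loss comes on top, and the documents give no figure for the intermediate class. Over symptomatic enrolled patients, even the direction of the error is open. Because this concerns the primary endpoint and the headline conclusion, the wording should not stand.

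**What to change.** 1. Restate the primary endpoint and the conclusions as PoPH detected by symptom- and UCG-triggered screening, and name one denominator.
2. If the denominator is all questionnaire respondents, account for refused consent and UCG not done, call the estimate a lower bound, and add a sensitivity analysis dividing it by first-step sensitivity from 0.40 to 1.0. If uptake is handled by extrapolating from those who had UCG, state the assumption that they represent those who did not. Do not apply the division to a symptomatic-only denominator.
3. Treat patients with intermediate-probability UCG who are not catheterized as unverified rather than negative, and show bounds with none and with all of them having PoPH.
4. Label the survival result as that of symptomatic, screen-detected PoPH, with no claim on the direction of bias.
5. Reconcile the referral wording of the Abstract with that of Trial design and follow-up. Which trigger applies is for the investigators to state.

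The cost is a more modest headline claim and one extra analysis. No added procedures are needed.
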